#### 15.4. Procedures for handling missing, rejected, and abnormal data

Cases in which the tests and data collection described in this research protocol could not be performed for any reason will be omitted or rejected, and in principle, the missing values will not be supplemented. In addition, for outliers such as outliers, all data are used in the analysis in principle, but in the case of exclusion, the reason for exclusion is recorded. The handling of missing values and abnormal data is described in the statistical analysis plan.

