### 13. Evaluation items

#### 13.1. Efficacy endpoints

##### 13.1.1. Primary endpoint (primary endpoint)

<PART1>

Comparison of 30-second walking distance between SMA and sham stimulation

<PART2>

Comparison of 30-second walking distance between M1 and sham stimulation

[Rationale for setting]

As a basis for setting the primary endpoint, patients with sloping feet may have a decrease in walking speed, but in severe cases, they may not be able to walk at all when walking, and they may not be able to achieve almost any walking distance. Even in such a case, if the walking distance is taken as the

primary endpoint, it can be left as data. On the other hand, the 10-m walking time set as a secondary endpoint may not be available for such severe cases, and the patient may have to be excluded. Therefore, walking distance was set as the primary endpoint.

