##### 15.2. Population to be analyzed

In principle, the target population for efficacy analysis of this study is the target population for

Intention-to-treat (ITT) analysis, which covers all cases, but the following subjects are excluded from the study population.

- 1) Those who do not meet the inclusion criteria
- 2) A person who has never taken measurements with a device.

The target population, including subjects who have undergone tDCS stimulation at least once, will be analyzed as the target population for safety analysis.

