#### 15.3. Aggregation and Analysis Methods

The background of the study subjects is calculated and aggregated by calculating the mean value and standard deviation for continuous variables, and the frequency and proportion for categorical variables. If the continuous variable clearly does not follow a normal distribution, transform the variable appropriately, such as a logarithmic transformation, and summarize it by mean and standard deviation, or use the median and interquartile ranges as descriptive statistics.

The primary endpoint, the difference in walking distance between 30 seconds after tDCS stimulation and sham stimulation, will be assessed using a single-sample t-test or a Wilcoxon signed rank test.

For the difference in secondary endpoints, 10 m natural walking time and number of steps, Timed Up and Go test, and 360° rotation test after tDCS stimulation and sham stimulation. Evaluate with a one-sample t-test or a Wilcoxon signed rank test.

together with

Video recording of the gait state is performed to objectively analyze the change in the gait state from the perspective of a specialist (neurologist, rehabilitation doctor) when improvement is obtained.

For safety, frequency and proportion (for all subjects) for each adverse event will be evaluated.

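### Section 15.4 treats a test not performed because of freezing as missing, so unable-to-able and able-to-unable changes are lost from the secondary analyses, and on a literal reading an obtained primary value is lost too

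*Protocol*

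**What the plan says.** **Section 15.4** sets the rule: "Cases in which the tests and data collection described in this research protocol could not be performed for any reason will be omitted or rejected". It adds that "in principle, the missing values will not be supplemented", and ends: "The handling of missing values and abnormal data is described in the statistical analysis plan".

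**Section 13.1.1** explains why 30-second distance is primary. It expects that "in severe cases, they may not be able to walk at all when walking". Once distance is taken as the "primary endpoint, it can be left as data", such a patient is kept. By contrast, "the 10-m walking time set as a secondary endpoint may not be available for such severe cases, and the patient may have to be excluded".

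**Section 15.2** bases efficacy on "Intention-to-treat (ITT) analysis, which covers all cases". It lists two exclusions: failing the inclusion criteria, and never having been measured with a device. Inability to perform a test is not among them.

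**Section 15.3** analyses the stimulation-minus-sham difference in each endpoint. The primary difference "will be assessed using a single-sample t-test or a Wilcoxon signed rank test", and the secondary endpoints are handled in the same way.

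**The concern.** In a trial of freezing of gait, being too frozen to finish a test is the worst result the test can show. It is not an accident of data collection. Section 15.4 puts it in the same class as equipment failure or withdrawal.

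The protocol makes such inability foreseeable. Section 13.1.1 describes patients who cannot walk, and Section 10.3 has patients with large fluctuations assessed in the drug-off state, when symptoms are severe.

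Two things are at stake:

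- On the timed tests, the largest possible improvement (unable after sham, able after stimulation) and the largest possible deterioration (the reverse) both disappear. The estimate then describes milder patients than those the trial is about, and a harm signal can be lost where freezing is worst.
- If the rule removes whole cases, it would also discard primary distances that Section 13.1.1 was written to preserve.

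**Working it through.** The protocol gives no alpha, power, effect size or SD, and Section 15.1 sets the 20 patients on feasibility, so there is no planned power figure to reproduce. The check sets the sections against each other and then shows the effect on assumed inputs.

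**1. Which values survive on a secondary test.** The analysed quantity for patient i is D_i = Y_i(stimulation) - Y_i(sham). It needs both values.

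| After sham | After stimulation | D_i | Clinical content | Under 15.4 |
|---|---|---|---|---|
| able | able | defined | change in seconds or steps | analysed |
| unable | able | undefined | largest improvement | lost |
| able | unable | undefined | largest deterioration | lost |
| unable | unable | undefined | no change | lost |

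This holds whether 15.4 omits the missing endpoint or the whole case, because nothing is supplemented.

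**2. What happens to the primary value.** Take a patient who attempts the 30-second walk, covers about 0 m, and cannot finish the 10-m walk.

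- Per-endpoint reading: the distance stays and only the 10-m result is omitted. This agrees with 13.1.1 and 15.2.
- Case-level reading: the patient leaves every analysis. This contradicts 13.1.1 and adds a third exclusion to the two in 15.2.

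Sections 15.1 and 15.2 use the word case for a patient, so the case-level reading is the literal one. It could also reject PART 1 data from someone who does not go on to PART 2. Under Section 5.3 that step takes into account whether gait evaluation is feasible.

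**3. Direction of bias if whole cases are dropped (assumed inputs).** Let s be the share unable, m the mean gain in the others, r the share of the unable who recover, and G their gain. Then mean with all kept = (1 - s)m + s·r·G, and mean with the unable dropped = m. Take s = 0.20, m = 1 m, G = 10 m.

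- r = 0.5: 0.8 × 1 + 0.2 × 0.5 × 10 = 1.8 m kept, against 1.0 m dropped (simulated: 1.79 and 0.99).
- r = 0: 0.8 × 1 + 0 = 0.8 m kept, against 1.0 m dropped (simulated: 0.79 and 0.99).

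Dropping understates the gain in the first case and overstates it in the second.

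**4. Power on a timed test (assumed inputs).** Simulation of 20 patients, signed-rank test, two-sided 0.05. Differences in able patients are N(effect, 1). Unable-to-able counts as the best-ranked improvement and unable at both as zero. No able-to-unable patients are modelled.

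| Effect | Unable after sham | Of these, able after stimulation | Dropped | Worst-ranked |
|---|---|---|---|---|
| 0.3 SD | 25% | 0% | about 18% | about 18% |
| 0.3 SD | 25% | 25% | about 18% | about 32% |
| 0.3 SD | 25% | 50% | about 17% | about 45% |
| 0.3 SD | 10% | 50% | about 22% | about 33% |
| 0 | 25% | 0% | about 5% | about 5% |

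A repeat with Pratt's handling of zero differences gave the same pattern, with slightly lower power in the worst-ranked column. Nearly all of the gap comes from the assumed share who become able.

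**The case against.** The strongest reply is that 15.4 need not mean whole-case deletion. Its heading concerns data. The same sentence goes on to speak of missing values, which would be pointless if the case had already gone. Exclusion of subjects is governed by 15.2. The rationale in 13.1.1 makes sense only if failing the 10-m walk leaves the distance in the analysis. A reader might infer from the literal wording that severe freezers are certainly removed from the primary analysis. The documents do not support that: an attempted walk of about 0 m is a performed test, and 13.1.1 means its value to be kept. This part of the reply stands, and the primary-endpoint problem is therefore conditional.

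It can also be said that 13.1.1 openly accepts the loss on the 10-m walk, that the study is exploratory and not powered, and that 15.4 leaves the handling of missing values to a statistical analysis plan that is not shown. These points limit the weight of the concern. They do not remove it:

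- Accepting the loss does not make it independent of outcome, and 13.1.1 does not mention the other two tests.
- Section 15.4 fixes omission without supplementation before it defers. A plan that follows it inherits the rule, and one that departs from it conflicts with the protocol.

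Lastly, the standard signed-rank test discards zero differences, so worst-ranking alone would drop patients unable under both conditions. That is correct, and the fix has to name a method for zeros.

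**Conclusion.** The point holds for the secondary endpoints under either reading: 15.4 excludes patients according to the outcome and loses changes in both directions on the 10-m walk, Timed Up and Go and 360-degree turn. For the primary endpoint it holds only if the rule is applied to whole cases. That reading is plausible, and it would contradict 13.1.1 and 15.2, but the text does not settle it.

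The size and direction of the bias cannot be derived from the documents, which give neither the share of patients unable to perform a test nor the share who change. A reader might take the 17% against 45% comparison as the power the trial loses. It is not: with none restored there is no gain at all, and the figures concern a timed secondary test on assumed inputs. Nor can one conclude that the rule works against stimulation, since it can also flatter it.

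This is a wording fault with a cheap remedy and should be corrected before analysis. The choice between the t-test and the Wilcoxon test for the primary endpoint is a separate matter.

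**What to change.** Amend Section 15.4, with matching text in the statistical analysis plan, to state that:

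1. Omission is per endpoint and per PART, never of the whole case.
2. An attempted 30-second walk without progress is recorded as 0 m and kept, as 13.1.1 intends.
3. Gait-related inability on the 10-m walk (time and steps), Timed Up and Go or 360-degree turn is an outcome ranked worse than any completed value. Unable after sham and able after stimulation is the best-ranked improvement, the reverse is the worst-ranked deterioration, and unable at both is a zero difference.
4. These endpoints are analysed by a signed-rank test with a named method for zero differences, for example Pratt's. Counts of able and unable patients are reported by condition.
5. Only non-gait reasons, such as equipment failure or withdrawal, count as missing.

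Reconcile the result with Sections 13.1.1 and 15.2. Any power illustration should be labelled as assumed and shown over a range.

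The cost is wording, plus recording the reason for each test not completed. The downside is that mean differences in seconds or steps become descriptive, in completers only.

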#### 15.5. Procedure for modifying the original statistical analysis plan

If there is a change from the original statistical analysis plan, the research protocol or statistical analysis plan will be revised and explained in the summary report of the clinical study.

#### 15.6. Interim analysis and early discontinuation of the study

No interim analysis was performed in this study.

#### 15.7. Other, Exploratory Analysis

Depending on the results of the study, an exploratory analysis such as a subgroup analysis may be performed. The objectives, items, methods, and results of the analysis are described in the final report.

#### 16. Viewing of original documents, etc.

The Principal Investigator and the Conducting Medical Institution shall make all clinical research-related records, including source materials, directly available for inspection during monitoring and auditing related to clinical research and investigations by accredited clinical research review boards and regulatory authorities.

## 17. Quality Control & Quality Assurance

### 17.1. Monitoring & Auditing

#### 17.1.1. monitoring

##### Implementation Structure

The monitoring of this study will be carried out by a person belonging to the Clinical Research and Clinical Trial Center of Juntendo University Hospital, Juntendo University School of Medicine, designated by the principal investigator in accordance with the monitor designation form.

Contact: [name]  
TEL (direct) [name]

##### Monitoring Methods

The monitoring of this study will be carried out by central monitoring. The monitor will prepare a monitoring report and submit it to the principal investigator within one month after the monitoring is conducted.

○Facilities subject to monitoring

Juntendo University School of Medicine Juntendo Hospital Neurosurgery

Juntendo University School of Medicine Juntendo Hospital Department of Neurology

##### Timing of monitoring

The study will be monitored once at the end of the study

##### Items to check for monitoring

The monitor checks the following:

- ① Patient enrollment status: Number of registrations, cumulative
- ② Eligibility: Patients who may be ineligible
- ③ Pre-treatment background factors (basic information of study subjects)
- ④ Between/after study treatment, discontinuation, and reason
- ⑤ Whether or not there is a non-conformity, and what it is
- ⑥ Whether or not there is a malfunction of the equipment, such as illness, etc., its contents, and the status of response
- (7) Other issues related to the progress of testing and safety

#### 17.1.2. audit

##### Implementation Structure

The audit of this study will be conducted by a person designated by the principal investigator with an auditor designation letter at the appointment of the Director of the Clinical Research Compliance and Governance Promotion Office, Clinical Research and Clinical Trials Center, Juntendo University Hospital.

Contact: [name]  
TEL (direct) [name]

##### How to Conduct an Audit

(1) The audit of this research will be conducted by visiting the facility.

○Facilities subject to audit

▪ Department of Neurosurgery, Juntendo University School of Medicine

▪ Department of Neurology, Juntendo University School of Medicine

(2) Direct inspection (SDV) shall be carried out in accordance with the procedures of the medical institution.

##### When to conduct an audit

Audits of this research will be conducted at the end of this research and when other needs arise. The auditor shall submit the audit report to the principal investigator within one month after the completion of the audit.

- Audits to be conducted at the end of the research

After the monitoring of this study is completed, an audit will be conducted.

- Audits to be conducted when the need arises

The audits to be conducted when necessary for this research are as follows.

- (A) When a disease report is submitted to the Minister of Health, Labour and Welfare
- (B) When serious non-conformity\* with the law, enforcement regulations, or research planis discovered.
- (C) In addition, when the principal investigator deems it necessary.

\* Serious non-conformity is defined as one that affects the human rights, safety, progress of research, and reliability of results (e.g., non-compliance with inclusion/exclusion criteria, discontinuation criteria, etc.). In order to avoid immediate danger to the subject, those who did not comply with the research plan for other medical compelling reasons are not included.

#### Audit Checks

The audit of this study will confirm the following items.

- Documents related to the procedures of the Clinical Research Review Board
- Consent form obtained from the research subject, withdrawal of consent form
- List of research subject identification codes
- Storage and management status of personal information
- Confirmation of case eligibility
- Status of medical examinations and examinations
- Number of cases of discontinuation of research and reason for discontinuation
- Presence of equipment malfunctions, such as diseases, contents, and response status
- Presence, content, and status of non-conformity (including serious non-conformance) with the Clinical Research Act or research plan
- Monitoring results and storage status of monitoring reports
- Other matters required by the principal investigator

#### 17.2. Data Management

In this study, we use CRF and REDCap as a management tool for data management. After the data is fixed, [name], who is in charge of statistical analysis, performs statistical analysis.

#### 18. Ethical Considerations

##### 18.1. Rules to be observed

All persons involved in this research shall carefully read and understand the contents of the "Declaration of Helsinki of the World Medical Association," the "Ethical Guidelines for Medical Research on Human Subjects," and the "Clinical Trials Act," which all medical research involving human subjects should comply with.

##### 18.2. Protection of personal information and privacy of research subjects

Persons involved in research shall comply with applicable laws and ordinances regarding the protection of personal information of research subjects. In addition, the relevant parties shall make every effort to protect the personal information and privacy of the research subjects, and shall not divulge personal information obtained in the course of conducting this research without a justifiable reason. The same shall apply even after the person concerned has retired from the position.

When handling personal information related to research conduct, each participating facility (personal information manager, etc.) shall manage it with a research ID that is not related to personal information, and give due consideration to the confidentiality of the research subject. The correspondence table prepared is strictly managed by the principal investigator in a locked locker in the neurosurgery laboratory.

## 19. Explanation and method of obtaining consent from the subject of clinical research

### 19.1. Summary of the burden and anticipated risks and benefits to the study subjects

Participation in this study will not create any new financial burden on the study subjects.

There is no projected direct benefit for the study subjects to participate in the study, and the same applies to the disadvantages.

### 19.2. Projected Profits

Although it is unclear whether the study participants will benefit from participating in this study, the results of this study may contribute to future medical advances by improving the improvement of refractory feet and applying to rehabilitation, for which there is currently no effective treatment.

There are no new costs associated with the treatments being tested in this study. In addition, since all medical expenses, including drug costs, during the study period of the study subjects are paid by the patient's insurance and the patient's own expenses, there is no special medical or economic benefit that can be obtained by the study subjects by participating in the study.

### 19.3. Anticipated Dangers and Disadvantages and Measures to Minimize Them

Transcranial direct current electrical stimulation is based on the recommendation from the committee of the Japanese Society of Clinical Neurophysiology that stimulation at an intensity of 3 mA for up to 30 minutes is safe, and stimulation is performed within this range. In fact, the stimulator used in this study is actually a commercially available device, and the maximum output is 2.0 mA, and it is designed so that stimulation cannot be used for more than 20 minutes per day.

However, as an adverse event, it is expected to cause some tingling in the scalp. If the stimulus is unpleasant, respond by reducing the intensity of the stimulus. In addition, if the subject complains of discomfort such as itching, headache, or burning, the stimulation should be stopped immediately.

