#### 5.3. Clinical Research Outline

In the tDCS stimulation used in this study, it is difficult to blind the presence or absence of irritation because the patient feels discomfort in the scalp when the stimulation is actually performed. On the other hand, in order to eliminate the effects of wearing the tDCS device even in a state where no stimulation is performed (sham stimulation), evaluation is performed with sham stimulation and actual stimulation. In general, patients with Parkinson's disease have large motor fluctuations in symptoms due to drug therapy, so the patient's condition may vary depending on the timing of the examination. Therefore, when conducting a stimulation test, it is considered that an appropriate evaluation cannot be performed unless the sham stimulation and the actual stimulus are evaluated as a set.

In this study, we evaluated the efficacy and safety of SMA stimulation for sham stimulation in PART 1 and the efficacy and safety evaluation of M1 stimulation for sham stimulation in PART 2. Two tests will be conducted. In PART 1, participants will first practice various gait assessment without any intervention. Next, the tDCS device is worn on the head for 20 minutes in a resting state (sham stimulation: no actual stimulation), and then the device is removed and gait evaluation is performed. Thereafter, the tDCS device is attached again, SMA stimulation is actually performed at 2 mA for 20 minutes, and then the

device is removed and gait evaluation is performed. This is PART 1. At this point, a decision is made on whether or not to move to PART 2 in consideration of the patient's condition and the feasibility of gait evaluation for each patient. If it is judged that it is possible to migrate, the test of PART 2 will be conducted at an interval of at least 6 hours after the implementation of PART 1. In PART 2, as in PART 1, various gait evaluations are first practiced without any intervention, and then gait evaluation is performed after 20 minutes of sham stimulation with a tDCS device. After that, the tDCS device is attached again, and M1 stimulation is actually performed at 2 mA for 20 minutes, gait evaluation is performed, and PART 2 is completed.

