## 9. Treatment/Intervention for Clinical Study Subjects

### 9.1. Overview of Pharmaceuticals Used in Clinical Research

#### Transcranial Direct Current Electrical Stimulator (tDCS Instrument)

Brand name : Halo Sport 2

manufacturer : Halo Neuroscience

**Overview** : It is a commercially available headphone-type tDCS device. Three pairs of stimulation pads are attached, which are attached to the crown of the head (M1). The midline pad is on the upper and lower limbs on both the left and right sides, as well as the trunk. The pads on both sides are designed to perform anode stimulation in the left and right hand finger areas. Originally for athlete training and musical instrumentsIt is a device developed to improve skills, has a maximum output of 2.0 mA, and is operated with a smartphone application.1timeIt is designed so that stimulation cannot be done for more than 20 minutes.In addition, it is small and lightweight, and it is possible to stimulate the patient while actually walking.

In this study, with normal attachment to the crown of the head, stimulation from the midline pad M1 stimulation of the upper and lower limbs on both sides and the trunk is possible, and from that state both sides SMA stimulation is possible by shifting in front of 3 cm around the coronal suture. In sham stimulation, All you have to do is attach the device to each part. It doesn't actually stimulate.

**Significant side effects:** This device is actually a commercially available tDCS device, which is widely used by the general public, and its safety is ensured by the design of the stimulator. Stimulation with this device is performed within the scope of the recommendation from the committee of the Japanese Society of Clinical Neurophysiology that stimulation at an intensity of 3 mA for up to 30 minutes is safe, so it is unlikely to cause serious side effects. However, as a side effect, it is expected that you will feel some tingling in the scalp.

[figure not shown]

Halo Sport 2

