### 10.2. Timing and duration of interventions such as medication, surgery, and examinations

After this registration, 2 sets of walking evaluations will be performed in 1 to 2 days (2 walking evaluations in PART 1 and 2 walking evaluations in PART 2, 4 times in total). After the first set of walking evaluations, there will be a wash out period of at least 6 hours.

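### Section 19.3 says the device cannot stimulate for more than 20 minutes per day, yet the schedule permits two 20-minute active stimulations on one day

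*Protocol*

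**What the plan says.** Protocol section 19.3 sets out the anticipated dangers and the measures against them. It refers to a professional recommendation on stimulation strength and duration (3 mA, up to 30 minutes), gives the device's maximum output as 2.0 mA, and adds that "it is designed so that stimulation cannot be used for more than 20 minutes per day".

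Section 9.1 describes the same device and gives the cap as "1timeIt is designed so that stimulation cannot be done for more than 20 minutes". The text is damaged at the point where the unit should stand. It names no daily cap.

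On the schedule, section 5.3 states for PART 1 that "SMA stimulation is actually performed at 2 mA for 20 minutes" and for PART 2 that "M1 stimulation is actually performed at 2 mA for 20 minutes". It places PART 2 "at an interval of at least 6 hours after the implementation of PART 1". Section 10.2 says that "2 sets of walking evaluations will be performed in 1 to 2 days", again with a gap of 6 hours or more. Section 10.3 repeats that interval, and the schedule table in 12.1 requires only that more than 6 hours have passed since PART 1 ended. No section puts PART 2 on a later calendar day.

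**The concern.** The daily limit appears in the part of the protocol that explains how participants are kept safe, and it is described as something built into the device. The schedule permits a course of stimulation that such a device could not deliver. The two statements cannot both describe what will happen to a patient who completes both PARTs in one day.

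What is at stake depends on which statement is wrong:

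- If the limit is per day, the M1 stimulation of a same-day PART 2 cannot be given in full. M1 versus sham is one of the two primary comparisons (13.1.1). The target is 20 patients (15.1), and fewer may reach PART 2, because 6.3 makes the transition a case-by-case decision.
- If the limit is per use, the review board has been told of a safeguard that does not exist, and a same-day participant would receive twice the daily exposure that 19.3 presents as impossible.

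**Working it through.** The 20-minute limit is a device specification, so it cannot be derived from other figures in the protocol. The check is whether the permitted schedule stays within it.

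**Inputs**

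- Limit in 19.3: 20 minutes per day.
- Active stimulation in PART 1 (SMA): 20 minutes (5.3, 10.3).
- Active stimulation in PART 2 (M1): 20 minutes (5.3, 10.3).
- Current during sham: none. Section 5.3 describes it as "sham stimulation: no actual stimulation", and 9.1 agrees. Sham adds 0 minutes.
- Minimum gap between PARTs: 6 hours (5.3, 10.2, 10.3, 12.1).
- Duration of one test: about 1 hour (10.3).
- Span of both PARTs: 1 to 2 days (10.2).

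**Step 1: is a one-day schedule realistic?** Elapsed time = first test + minimum gap + second test = 1 + 6 + 1 = about 8 hours. It fits in one day, and 10.2 expressly allows it.

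**Step 2: active minutes on that day.** PART 1 sham + PART 1 active + PART 2 sham + PART 2 active = 0 + 20 + 0 + 20 = 40 minutes.

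**Step 3: compare with the limit under each reading.**

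| Reading of the 20-minute limit | PARTs on one day | PARTs on two days |
|---|---|---|
| Per day (19.3) | 40 against 20: over by 20 minutes, ratio 40/20 = 2 | 20 on each day: within |
| Per use (apparent sense of 9.1) | 20 per use: within | 20 per use: within |

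Under the per-day reading the one-day option fails. Under the per-use reading every schedule passes, but the words about a day in 19.3 are then wrong. Neither reading leaves both 19.3 and the one-day option standing.

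**The case against.** Several points on the other side are sound.

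- Sections 9.1 and 19.3 do not strictly contradict each other. A device capped at 20 minutes per day is also capped at 20 minutes per use. The wording in 9.1 is also too damaged to carry much weight. The conflict is between 19.3 and the one-day schedule, and it does not need 9.1.
- PART 2 can be done on the second day within 10.2, so a refusal by the device need not cost the data.

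A reader might go further and infer that locked-out sessions would be analysed as M1 stimulation, diluting the second primary comparison in proportion to the share of patients treated on one day. The documents do not support this. The device is run from a smartphone application (9.1), subjects are told whether they are being stimulated (7.3), and 5.3 says that real stimulation is felt on the scalp. A stimulation that failed to start or stopped early would very probably be noticed. Section 15.4 says that cases in which the planned tests or data collection could not be performed are omitted, without imputation, and nothing says that an undelivered stimulation counts as delivered. The share treated on one day is not given, so no dilution can be calculated.

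A reader might also infer that patients are misinformed, or that the 30-minute recommendation is exceeded. The consent document is separate (19.4) and not shown. Sections 9.1 and 19.3 do not say whether the 30 minutes applies per session or per day.

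These points narrow the consequences. None of them reconciles 19.3 with the one-day option.

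**Conclusion.** The contradiction stands. A schedule that the protocol allows plans 40 minutes of active stimulation in one day, against a limit of 20 minutes per day stated as a safeguard in 19.3. Either the one-day option is not fully deliverable with this device, or the safety statement is wrong. The documents do not show which.

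The finding is confined to patients with both PARTs on one day. It takes a day to mean a calendar day and assumes that both stimulations run their planned 20 minutes. It is an inconsistency in the text that bears on safety and feasibility. No bias in the primary analysis is shown.

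**What to change.** Confirm from the device's specification what the 20-minute limit refers to, including how a day is counted if the limit is daily. Then reconcile 5.3, 9.1, 10.2, 10.3, 12.1 and 19.3 so that the safety statement and the permitted spacing of the PARTs agree, and repair the damaged wording in 9.1. Check whether the explanation and consent document repeats the daily limit, and align it if so. Which limit and spacing are right is for the investigators and the review board.

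As an optional check, record the minutes of stimulation delivered in each session. Section 25 already provides for records of the date, time and place of use for each subject, so this would be one more field.

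The cost is a wording amendment to the protocol, possibly to the consent document as well. If the limit proves to be daily, fewer patients may be able to complete both PARTs on one day.
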